### Outcome Measures

#### Primary outcome measures

Using a checklist including common drug problems, the prevalence of DRP in patients of control and intervention pharmacists will be determined at base-line and at 12 months by a team of independent clinical pharmacologists. The identification of drug problems by community pharmacist will be assessed on the basis of a structured interview of the patient and the medication overview of the patient registered in the pharmacy information and administration system.

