##### Cognitive behaviour treatment

Patients randomised to the intervention group will also receive cognitive behaviour treatment (CBT) at baseline and 1, 3, 6, 9 and 12 months by a pharmacy technician, with help of a structured interview protocol and with use of communication and motivational interviewing skills at home or in the pharmacy. The first session will be within one week of inclusion in order not to delay participant program admission. During these sessions the result of the medication review will be discussed with the patient. The patient will be informed about the effects, side effects and use of the drugs. Patients will be counselled according to the motivational interviewing principle to sustain or improve their drug adherence. The patients understanding of his or hers condition and its treatment are considered when appropriate. If possible, home supplies of drugs are checked and rationalised at each visit. All patients receive a written outline of their drug regimen. Cancelled and redundant drugs are taken in. During the session, over the counter remedies will be included in the medication review. All sessions are done by pharmacist technicians with help of a structured protocol. The patient visit will take 30-60 minutes.

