##### Training course pharmacists

All participating intervention pharmacists will participate in a one day medication review training course. During this training session the background of medication review will be explained. The use of Medication Evaluation Profiles will be explained. Furthermore, the way the PCNE DRP-score form should be used will be explained.

To pilot test the interrater variability of the PCNE DRP-score form and the efficacy of the medication review training all participating pharmacists (controls and intervention pharmacists) will receive 5 medication overviews of test-patients with additional information about clinical notes approximately three months before the medication review training session. The results of the medication reviews will be evaluated by a specialist in medication review.

When intervention pharmacists have completed the training course in medication review, all pharmacists (control and interventions) will be asked to review five new test-patients. The intervention pharmacists are expected to detect more DRPs afterwards than control pharmacists who did not receive a special training in medication review. The results of the medication reviews will be evaluated by the same specialist as before.

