##### Training pharmacy technicians

All intervention technicians will participate in a two days training course of motivational interviewing and a one day course of problem solving treatment. During these training sessions pharmacy technicians will be lectured about communication skills such as Motivational interviewing and Problem solving treatment skills by a specialized psychologist on this subject. In addition pharmacy technicians will receive coaching on the job. Video tapes of interviews with patients will then be recorded and reviewed by two independent researchers using the Motivational Interviewing Treatment Integrity Code score method to evaluate the quality of the motivational interviewing skills of the pharmacy technicians.

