#### Control Group

Patients of control pharmacists will receive usual care according to the Dutch Pharmacy Standard (Table 1). Furthermore, patients are visited once by a pharmacy technician and asked about possible drug related problems. These problems will be registered for scientific use only.

**Table 1 T1:** Usual care, according to the Dutch Pharmacy Standard

1	Preceding the release check, prescriptions are routinely checked for drug interactions and contra-indications by the PAIS.
2	Discharge medication is delivered at the patients' home or is picked up by the patient or carer in the pharmacy.
3	Drugs are routinely delivered with a drug information leaflet but patients often are also handed supplementary personalized PAIS-generated information letters on newly prescribed drugs.
4	When the discharge medication is collected from the pharmacy, the patient or carer is also provided with additional oral information about newly prescribed drugs. This includes an explanation of the drugs' actions, their use and of possible side effects.

First edition of 1996. The current (2nd) edition was introduced in 2006 (KNMP, The Hague).

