There are several practical limitations associated with performing medication review. Detecting and solving drug related problems by health care workers such as community pharmacists is a time consuming process [35]. In order to make any changes in the drug regimen, the pharmacist has to contact the general practitioner first, which is time consuming. Furthermore, community pharmacists have to communicate the changes that are made with their patients. Because of their busy daily schedules, it may be possible that pharmacists do not find that medication review has a priority. Another major limitation is the possible bias in the detection and solving of DRPs by the different community pharmacists since all pharmacists have different experiences in performing a medication review. Some pharmacists will therefore identify more or less drug related problems than others, depending on the limited time. In addition, another limitation of the intervention is that the performance of CBT might differ between pharmacy technicians because of the interview skills they have. It is therefore difficult to decide whether all patients receive the same therapy sessions. We will try to reduce the differences between the pharmacy technicians, by using a structured interview protocol and motivational interviewing and problem solving treatment courses. A major strength is by combining medication review and CBT sessions can lead to a possible improvement of detection of drug related problems. The CBT sessions with patients discharged from the hospital will be helpful in detecting drug problems such as side effects and non-compliance, and thus lead to a better communication between the community pharmacy and patient.

A limitation of the study design is that there is no literature available that describes an evidence based method that can be used by pharmacists to report the quality of the pharmacotherapy or how to detect and solve drug related problems. However, we will apply in this study a method of prescription problems which we can test on feasibility and effectiveness. Strength of this study design is that it is a RCT.

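### One drug-problem visit for control patients does not fit an interview-based primary outcome at baseline and 12 months, so the inputs to that outcome may differ by arm

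*Protocol article*

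**What the plan says.** **Outcome.** In the Protocol article, under Primary outcome measures, one checklist covers both arms ("Using a checklist including common drug problems, the prevalence of DRP in patients of control and intervention pharmacists"), and prevalence "will be determined at base-line and at 12 months by a team of independent clinical pharmacologists". The next sentence reads "The identification of drug problems by community pharmacist will be assessed on the basis of a structured interview of the patient", and adds the patient's medication overview held in the pharmacy system as a second source.

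**Control arm.** Under Control Group, "patients are visited once by a pharmacy technician and asked about possible drug related problems". No time is given for this visit, and no other control interview about DRPs is described.

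**Intervention arm.** Patients receive "cognitive behaviour treatment (CBT) at baseline and 1, 3, 6, 9 and 12 months by a pharmacy technician". On training: "All intervention technicians will participate in a two days training course of motivational interviewing and a one day course of problem solving treatment". The Discussion adds: "The CBT sessions with patients discharged from the hospital will be helpful in detecting drug problems such as side effects and non-compliance".

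**Planned effect and analysis.** Sample size assumes 30% with DRPs among control patients and a reduction of one third. Analyses plans multilevel regression and also refers to differences between groups in change.

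**Acknowledged limitation.** The Discussion accepts that pharmacists will differ in how many DRPs they find. It does not consider that this difference may follow the randomised arm.

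**The concern.** An interview-based outcome at two time points needs two interviews per patient. The control arm has one described contact. The intervention arm has six, two of which fall at the outcome time points and all of which are held by staff trained in interviewing. If what is rated comes from these contacts, the arms are measured with different instruments.

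The outcome section does not settle this. Its first sentence gives the determination to the independent pharmacologists, and its second speaks of identification by the community pharmacist. How the second feeds the first is not said, and neither is whether the raters know the arm.

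The intervention is meant both to find DRPs and to reduce them. If finding more of them counts in the outcome, a null result could hide a benefit. In the analysis of change, a positive result could arise from the timing of one visit.

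**Working it through.** **Step 1. The described contacts side by side**

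| | Control | Intervention |
|---|---|---|
| Outcome time points needing an interview | 2 | 2 |
| Described technician contacts | 1, time not given | 6 (baseline, 1, 3, 6, 9, 12 months) |
| Interview training described for technicians | none | 2 days + 1 day |

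Control arm: 2 − 1 = at least one outcome time point with no described interview.

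**Step 2. Inputs for the size**

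The true rates come from Sample size: 30% control, and 0.30 × (1 − 1/3) = 20% intervention. The article gives no detection rates, so there is no figure of its own to reproduce. The rates below are assumptions, shown over a range. The formula is observed prevalence = true prevalence × detection, with no false positives.

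**Step 3. Comparison at 12 months**

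| Detection, control / intervention | Observed control | Observed intervention | Difference |
|---|---|---|---|
| 90% / 90% | 0.30 × 0.9 = 27% | 0.20 × 0.9 = 18% | 9 points |
| 80% / 80% | 0.30 × 0.8 = 24% | 0.20 × 0.8 = 16% | 8 points |
| 80% / 90% | 24% | 18% | 6 points |
| 70% / 90% | 0.30 × 0.7 = 21% | 18% | 3 points |
| 60% / 90% | 0.30 × 0.6 = 18% | 18% | 0 points |

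At 80% / 90%, imperfect detection alone would bring the true 10 points down to 8 or 9. The unequal part therefore accounts for 2 to 3 points (8 − 6 or 9 − 6), not 4.

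With no true effect (30% in both arms), equal detection gives a difference of zero. At 80% / 90% the result is 24% versus 27%, an apparent harm of 3 points. At 70% / 90% it is 21% versus 27%, an apparent harm of 6 points. More detection in the intervention arm thus always works against the intervention at 12 months.

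**Step 4. Change from baseline**

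Assume detection of 90% with an interview and 80% from the overview alone, true control prevalence constant at 30%, and intervention patients interviewed at both times. The intervention arm goes from 27% to 18%, a change of −9.

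- Control visit at baseline: 27% to 24%, a spurious −3. Difference in changes: 9 − 3 = 6 points.
- Control visit at 12 months: 24% to 27%, a spurious +3. Difference in changes: 9 + 3 = 12 points. The 12-month comparison is then 27% versus 18%, which is not distorted by unequal detection.
- Control visit at neither time: 24% to 24%. Difference in changes: 9 points, but the 12-month comparison is 24% versus 18%.

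With equal 90% detection the difference in changes would be 9 points. The sign of the error therefore depends on a visit date that the article does not give, and on whether the 12-month value or the change is analysed.

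**The case against.** The strongest reply is that the article sets a common assessment: one checklist, both arms, the same two time points, raters from outside the pharmacies. Nothing says that the control visit is the structured interview of the outcome section, or that no separate outcome interview takes place. Nothing says that the raters see session notes or review forms; the two listed sources are the interview and the medication overview. An article may also leave masking to the full protocol.

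Much of this stands, and it rules out several stronger readings that a reader might infer:

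- That the raters are unmasked. The article is silent on masking.
- That control DRPs at one time point will rest on the overview alone. That is one way to read the two sections, not a stated plan.
- That the primary comparison is biased. It is biased only if the raters work from the unequal inputs.
- That the article predicts unequal detection in the outcome when it says "The intervention pharmacists are expected to detect more DRPs afterwards than control pharmacists who did not receive a special training in medication review". That sentence concerns a training check on test-patients. The Discussion's remark on the counselling sessions is the relevant support.

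The reply does not remove the mismatch. A common checklist makes the rating equal, not the information that is rated. The only control contact about DRPs in the text cannot supply two interviews, and two parties are named as identifying DRPs with no rule on which one counts. These points concern what is collected and from whom, so they go beyond detail that an article would normally leave out.

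**Conclusion.** The concern holds in a conditional form. Control Group and Primary outcome measures are not reconciled, the source of the endpoint is ambiguous, and the described patient contacts differ by arm (one against six). If the raters use those contacts, the contrast mixes effect with detection. At 12 months the error goes against the intervention: 6 points instead of 8 or 9 under assumed detection of 80% and 90%, and no visible effect at 60% and 90%. For change from baseline it can go either way, 6 or 12 points against 9 in the example. The contact counts and the 30% and 20% come from the article. The detection rates, the absence of false positives and the constant control prevalence are assumptions. The documents support neither a firm size nor a firm direction.

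**What to change.** - Reconcile the two sections: say when the single control visit takes place, whether it is the structured interview, and who interviews control patients at the other time point.
- Make the independent pharmacologists' checklist rating the sole primary DRP measure.
- Base it on the same inputs in both arms at each time point. Where the interview is not available in both arms, use the medication overview alone in both.
- Exclude records from medication reviews and counselling sessions, remove pharmacy and arm identifiers before rating, and state whether the raters are masked.
- Report DRPs found by the community pharmacist as a process measure.

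The cost is the redaction of dossiers and somewhat less information per patient; no extra raters or visits are needed. Lower but equal detection still shrinks the difference: at an assumed 60% in both arms, 18% − 12% = 6 points. It keeps the one-third relative reduction, however, and shows no difference when there is none.

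New DRP items in the patient questionnaires would be a more debatable route. The Discussion says that inclusion is already done, so baseline items may come too late, and counselled patients may report problems more readily.

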#### Adherence with drug treatment

The 5-item self-report Medication Adherence Rating Scale (MARS) will be used to assess medication adherence [24].

#### Secondary outcome measures

##### Incidence of Re-hospitalization

The total incidence of hospital re-admissions possibly related to medicine during the study period is measured. The incidence of hospital admissions will be derived from general practitioners medical record and determined by self report. The relation to drugs will be derived using a list of selection criteria. Hospital admissions will be classified as related to drugs if:

▪ It is explicitly clarified in the medical notes that the admission is drug related. The specialist of the patient will be consulted to clarify the relation to drugs.

▪ The patients' physician, when asked, indicates that the admission was drug related.

▪ To classify the causality of the hospital admission to the drug, the Naranjo algorithm will be used. The Naranjo algorithm or Naranjo Scale is a questionnaire designed by Naranjo *et al *for determining the likelihood of whether an ADR is actually due to the drug rather than the result of other factors [25]. The causality will be determined by the project leader.

All participating patients are asked to complete 3 validated questionnaires during the research year. The first questionnaire will be sent to the patients one week before the first counselling visit of the pharmacist. The second questionnaire will be sent at 6 months, the third questionnaire will be sent at 12 months. It will take approximately 30 minutes to complete one questionnaire.

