## Background

Drug related problems (DRPs) are events or circumstances involving drug therapy that actually or potentially interfere with desired health outcomes [1]. Examples of DRPs are contra-indications, interactions, adverse drug reactions (ADR) and inefficacy of treatment. Causes for these problems can be prescription errors, non-compliance with treatment and the specific effects of drugs in patients. Factors that increase the risk of DRPs are polypharmacy, co-morbidity, aging, non-adherence and lack of coordination between different treating physicians.

An increased number of prescribed drugs (polypharmacy) strongly increase the risk of DRP. Runciman found a correlation between increases in medication use and rates of adverse drug reactions associated with hospitalization [2]. Another recent review of studies of the effect of polypharmacy on the health state of elderly people has shown that multiple drug use is a strong predictor of hospitalisations, nursing home placement, death, hypoglycaemia, fractures, impaired mobility, pneumonia and malnutrition [3]. Furthermore, Leendert et al suggest that elderly people have a higher risk of hospitalisation caused by DRP, especially if they use have 4 or more co-morbidity [4].

Elderly people >75 year seem at higher risk for hospitalisation caused by DRP [2]. A study conducted in the Netherlands examined the occurrence of hospitalisations that were related to medication. This study showed 12.793 acute hospital admissions per year of which 714 admissions were medication related and 332 of these admissions were preventable. They calculated that 19.000 hospital admissions per year were related to medication and were preventable [4]. Specific risk factors were the number of prescribing physicians [5] and the number of diagnoses [6], the number and combination of several (inappropriate) drugs [6,7] and the use of inappropriate drugs [8-11].

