Non-adherence is another risk factor for the occurrence of DRP. Assuming that drugs have been prescribed correctly, non-compliance may substantially affect the efficacy of treatment or even enhance the risk of side effects [12-14]. In the Dutch population 50% of the patients were shown to discontinue the use of chronic medication within one year after initiation. Discontinuation of chronic medication depended on the type of chronic medication and occurred frequently among patients who were using antihypertensive medication, cholesterol lowering drugs, anti-osteoporoses drugs, anti-rheumatic medications and antidepressants [15].

Hospitalisation can also be the cause of DRP. Hospitalisation and subsequent discharge are associated with discontinuity of care [16]. At the point of discharge the use of certain drugs may have been discontinued and the doses of others changed while new medication may have been added. In the Netherlands, pharmacists use a computerized system to detect drug problems among their patients. This system fails to detect all drug problems and does not provide information on problems with medication use, which elderly patients may experience. In the present study, pharmacists will perform a medication review on elderly patients discharged from the hospital. This medication review is a structured, critical examination of patient's medicines with the objective of reaching an agreement with the patient about treatment, optimising the impact of medicines, minimising the number of medication-related problems and reducing waste [17].

A systematic review conducted by Royal et al. concluded that there was evidence showing that pharmacist-initiated interventions including a medication review component are effective in reducing hospital admissions by 36%. Several studies have shown that cognitive behaviour treatment can be useful in improving medication adherence among patients [18,19]. Patients may benefit of changes in attitude to medication, resulting in increased compliance with drug use.

The present randomized controlled study aims to improve pharmacotherapy by means of combining two effective strategies including medication review and cognitive behaviour treatment. To our knowledge, the effect of combining both methods to minimize drug related problems and improve compliance among elderly patients discharged from the hospital has not been studied previously.

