### Objectives of this study

The objective of this study is to investigate the effects of a multifaceted intervention, existing of medication review and a CBT intervention for medication adherence, on the occurrence of DRP in elderly patients of 60 year and older discharged from the hospital using five or more drugs. The hypothesis of this study is that this multifaceted intervention will reduce the occurrence of DRP and improve compliance. The secondary objectives are to evaluate the effect of the intervention on: attitude to drugs, incidence of Re-hospitalisations related to medicines, functional status of the patient, quality of life. Moreover, the cost-effectiveness of this intervention will be analysed.

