### Costs effectiveness

Costs will be registered by the pharmacists in terms of time and material spent on the counselling of patients. Health care costs made by the patient will be assessed from a societal perspective using monthly costs calendars in which direct and indirect costs will be prospectively determined by the patient. The following costs will be included in the calendars.

▪ Visits to a General Practitioner (including home visits)

▪ Visits to a medical specialist

▪ Visits to a physiotherapist

▪ Hospitalisations or admission to a nursing home

▪ Informal care (from neighbours, family or friends)

▪ Alternative medical treatment.

Costs of prescription-only medication use will be derived from the pharmacy system.

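### Readmission is an outcome only when judged drug related; all-cause readmission, already collected, should be reported beside it

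*Protocol article*

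**What the plan says.** The Objectives list "incidence of Re-hospitalisations related to medicines" among the secondary aims. The section on incidence of re-hospitalisation defines the measure: "The total incidence of hospital re-admissions possibly related to medicine during the study period is measured". The Abstract carries the same restriction, and no section names readmission for any cause as an outcome.

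The data come in unrestricted: "The incidence of hospital admissions will be derived from general practitioners medical record and determined by self report". Relation to drugs is decided afterwards, from the medical notes with the specialist consulted, from the physician's answer when asked, and with the Naranjo algorithm, where the project leader determines causality. The cost calendars separately record "Hospitalisations or admission to a nursing home".

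The Background cites a systematic review as showing that "pharmacist-initiated interventions including a medication review component are effective in reducing hospital admissions by 36" per cent. The Discussion expects a lower risk of re-hospitalisation. Neither statement is confined to drug-related admissions. The Background also reports a Dutch study: "This study showed 12.793 acute hospital admissions per year of which 714 admissions were medication related and 332 of these admissions were preventable".

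**The concern.** Three things do not fit together.

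- **Rationale and outcome differ.** The benefit is argued for admissions as such, but only a labelled subset is counted.
- **The label can depend on the arm.** Under Medication review, drug-related problems found in intervention patients are discussed with the GP. Control patients are asked about problems once, and the answers are kept for scientific use only. A physician who has been through the patient's drug problems may call a later admission drug related more readily, or less readily. The article describes no blinding of the physician or the project leader for this step.
- **Few events are likely**, so a few labelling decisions could move the result.

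At stake is whether a difference in drug-related readmissions could be read as a change in readmission or only as a change in labelling. The all-cause count that would help to tell these apart is collected but is not an outcome.

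**Working it through.** The article gives no readmission rate, event count or power for this outcome, so there is no stated figure to reproduce.

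**Inputs.**
- Patients per arm: 342 / 2 = 171 (Sample size; ratio of one).
- Drug-related share of acute admissions: 714 / 12,793 = 5.58% (Background). Tripled as a sensitivity value: 16.7%.
- Effect: 36% reduction (Background).
- Patients readmitted within 12 months: 20-50%. This is an assumption.
- The share of admissions is applied to patients, each counted once. This is an approximation.

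**Step 1: expected control-arm patients** = 171 × proportion readmitted × share.

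| Readmitted | Any cause | Drug related, 5.58% | Drug related, 16.7% |
|---|---|---|---|
| 20% | 34.2 | 1.9 | 5.7 |
| 30% | 51.3 | 2.9 | 8.6 |
| 40% | 68.4 | 3.8 | 11.5 |
| 50% | 85.5 | 4.8 | 14.3 |

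**Step 2: power of the outcome as defined.** Fisher's exact test, two-sided 0.05, 36% fewer drug-related readmissions: 0.4-4% at the 5.58% share and 5-14% at the tripled share.

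**Step 3: power of all-cause readmission.** Two-proportion normal approximation with pooled variance under the null, n = 171 per arm, no allowance for clustering. Let p be the control proportion and s the share.

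- (a) The 36% applies to every admission: p versus 0.64p.
- (b) Only drug-related admissions fall: p versus p(1 − 0.36s). The ratio is 1 − 0.36 × 0.0558 = 0.98, or 1 − 0.36 × 0.167 = 0.94 at the tripled share.

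| Readmitted | (a) | (b) 5.58% | (b) 16.7% |
|---|---|---|---|
| 20% | 44% | 5.1% | 5.9% |
| 30% | 64% | 5.2% | 6.6% |
| 40% | 81% | 5.3% | 7.4% |
| 50% | 93% | 5.4% | 8.6% |

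Taking the protocol's 15% clustering loss as an effective 171 × 0.85 = 145 per arm, (a) becomes 38-88%.

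**Step 4: chance of a contrary all-cause direction when the drug-related benefit is real.** Under (b), this is Φ(−difference / standard error). At the 5.58% share it is 46% with 20% readmitted and 43% with 50% readmitted. At the tripled share it is 39% and 29%.

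**The case against.** The strongest reply is that a mechanism-specific secondary outcome is a legitimate choice in a trial about drug-related problems. It is stated consistently, the trial is sized on the primary outcome, and no power is claimed for readmission. That stands: nothing here is a contradiction or a miscalculation, and drug-related readmission should stay.

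Four stronger readings are tempting, and the documents do not support them.

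- **The article's own figures fix the number of events at a handful.** They do not. No readmission rate is given, and the 5.6% comes from acute admissions in another population. The Background says "elderly people have a higher risk of hospitalisation caused by DRP", and the outcome also takes in possibly related readmissions. At shares of 20-30% and 0.2-1.0 readmissions per patient-year (both assumed), the control arm would have about 7 to 51 events. Even at the top of that range, power for a 36% reduction is only about 48%.
- **All-cause readmission would be much better powered.** That holds only under (a). If the intervention prevents only drug-related admissions, a 36% all-cause fall needs a drug-related share of at least 36%, which means at least 171 × 0.20 × 0.36 = 12 to 171 × 0.50 × 0.36 = 31 such control patients. A 5.6% share and a 36% all-cause effect cannot then both hold.
- **The plan cannot detect net harm.** This goes too far. Hospitalisations enter the cost comparison, and RAND-36 and EuroQol are outcomes. An admission caused by a regimen change is also itself drug related and should be caught by the criteria.
- **A contrary all-cause direction should bar any conclusion on drug-related readmission.** By Step 4 such a rule would override a true benefit by chance in roughly 29-46% of trials.

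It can also be said that a condensed article may leave a supporting all-admissions tabulation to the full plan. That limits the weight of the point. But the article does fix the outcome's definition, in three places, and that definition is narrower than its rationale.

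**Conclusion.** The point holds as a modest improvement to a secondary outcome. The definition is narrower than the benefit the article argues for, although the wider data are already collected. It also rests on a judgement that one arm's procedures can influence. The documents do not show that labelling would in fact differ, or in which direction. The physician asked need not be the GP who discussed the drug problems.

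Few drug-related readmissions are likely: about 2-5 control patients at the 5.6% share and 6-14 at three times that share, given 171 per arm and 20-50% readmitted. These counts depend on an assumed readmission rate and a borrowed share.

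The case for all-cause readmission is that it matches the rationale and needs no relatedness judgement. It does not rest on power, which ranges from about 5% to 93% depending on whether the effect reaches admissions that are not drug related.

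**What to change.** Add all-cause hospital readmission within 12 months as a secondary outcome. Ascertain it in the same way in both arms, from the GP record and the questionnaires sent to all patients rather than from counselling visits, which are more frequent in the intervention arm. Keep drug-related readmission as its labelled subset. Report both by arm with 95% confidence intervals, claim no power advantage for either, and attach no rule that lets one result veto the other. If an expected event count is given, show it as a range with the assumed readmission rate and drug-related share.

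Cost: a change of wording and one extra analysis of data already collected. The downside is one more secondary result to report.
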